#### Randomization

2.4.1

In Phase II, all caregiver participants will be randomized into either Active VR group or Sham VR group using permuted block randomization with an allocation ratio of 1:1. All investigators will remain blind to the randomization scheme until each study participant is deemed eligible and signs the consent form. Once each participant is randomly assigned, the participant and the research team members will be aware of the group assignment status.

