### Data analysis and sample size estimation

2.6

For Phase I, a sample size of 12 is considered since this number is recommended to justify the study feasibility and precision of the mean and variance (53). To account for a 20% attrition rate, Phase I study will enroll up to 15 caregivers. To estimate a sample size for Phase II study, power analysis was performed based on the primary outcome. We used a two-sided hypothesis that the stress level will differ between Active VR group and Sham VR group. In order to detect a difference between Active VR group and Sham VR group, we will need 39 caregiver participants in each group and a total sample size of 78 based on an effect size of 0.6 and correlation of 0.80 between two time points from our previous stress reduction study (54), with 80% power and type 1 error of 0.05. To account for a 20% attrition rate, this study will enroll up to 94 caregivers.

In Phase I, feasibility, acceptability, and perceived restorativeness will be evaluated using descriptive statistics appropriate to the levels of measurement. Friedman test or linear mixed models will be used to test changes in stress measured weekly from Time 0 to Time 4. In Phase II, linear mixed repeated measures analysis will be used to analyze the effects of Active VR on stress compared to Sham VR. Any demographic covariates will be included in the model if significantly associated with the outcomes and significantly different between the two groups. All qualitative data, including written comments on open-ended questions and transcriptions of audio from the phone call follow-up and exit-interview, will be subjected to coding and qualitative data analysis.

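### Phase II demographic covariates enter only if significantly imbalanced and associated with outcome, so the rule almost always returns the unadjusted model; the power cost may be small, and no type I error inflation is shown

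*Protocol article*

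**What the plan says.** Section 2.6 of the protocol article (Data analysis and sample size estimation) gives the Phase II model in one sentence: "In Phase II, linear mixed repeated measures analysis will be used to analyze the effects of Active VR on stress compared to Sham VR". The next sentence gives the covariate rule: "Any demographic covariates will be included in the model if significantly associated with the outcomes and significantly different between the two groups". The two conditions are joined by *and*, so a covariate must pass both. The rule covers demographic variables only. It gives no list and no significance threshold, and it speaks of outcomes in the plural.

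Section 2.4.1 (Randomization) specifies "permuted block randomization with an allocation ratio of 1:1" and says that participants and the research team know the assignment once it is made. Nothing elsewhere in the article names a fixed covariate or overrides the rule.

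**The concern.** In a randomised comparison, a test of baseline difference at randomisation tests a null hypothesis already known to be true. What makes a covariate worth including is its relation to the outcome. Here that relation is not enough, because the covariate must also happen to be imbalanced.

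Two things are at stake:

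- **Precision.** Whatever demographic variables could add is usually thrown away.
- **Model choice.** The primary model is settled only after outcome and arm data have been inspected, by a team that knows the assignments. Each outcome may end up with a different covariate set, and the usual standard error takes no account of the selection.

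**Working it through.** **1. The plan's sample size.** Section 2.6 gives "39 caregiver participants in each group and a total sample size of 78", from "an effect size of 0.6 and correlation of 0.80 between two time points", two-sided, "with 80% power and type 1 error of 0.05". Using n per arm = 2(1.960 + 0.842)² × f / 0.6², where f is a variance factor:

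- f = (1 + 0.80)/2 = 0.90 (mean of two visits) gives 39.24; power at 39 per arm is 79.75%. This matches the stated figure within rounding.
- Other readings do not match: follow-up only 44, change score 18, baseline-adjusted 16.

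No reading uses a demographic covariate, so the rule does not affect the stated sample size.

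**2. How often a covariate enters.** The article gives no threshold; 0.05 is assumed for both tests. The imbalance test alone passes a covariate with probability 0.05, so it is excluded with probability 1 − 0.05 = 0.95. In simulation (39 per arm, independent normal covariates, R² 0.1 to 0.5), one prognostic covariate entered in about 3 to 5% of trials. At least one of five entered in about 6 to 19%.

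**3. Power and type I error without baseline stress in the model.** Single-outcome linear model, true difference 0.6 SD, 20,000 trials for power and 40,000 for type I error. R² is the assumed share of outcome variance explained by all the covariates together.

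| Covariates | R² | Power, rule | Power, pre-specified | Gap (points) | Type I error, rule |
|---|---|---|---|---|---|
| 1 | 0 | 0.743 | 0.739 | −0.4 | 0.051 |
| 1 | 0.1 | 0.743 | 0.784 | 4.1 | 0.047 |
| 1 | 0.2 | 0.753 | 0.829 | 7.6 | 0.044 |
| 1 | 0.3 | 0.760 | 0.877 | 11.7 | 0.042 |
| 1 | 0.5 | 0.763 | 0.955 | 19.2 | 0.035 |
| 5 | 0 | 0.738 | 0.714 | −2.4 | 0.051 |
| 5 | 0.1 | 0.737 | 0.760 | 2.3 | 0.047 |
| 5 | 0.2 | 0.737 | 0.804 | 6.7 | 0.045 |
| 5 | 0.3 | 0.739 | 0.855 | 11.6 | 0.043 |
| 5 | 0.5 | 0.753 | 0.949 | 19.6 | 0.039 |

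Unadjusted power was 0.741 to 0.750 throughout, so the rule is close to no adjustment. Pre-specified adjustment held type I error at 0.048 to 0.052.

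The upper end comes from a separate run (0.5 SD difference, 6,000 trials):

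- Two covariates at r = 0.4 (R² = 2 × 0.16 = 0.32): 59.3% against 74.5%, a gap of 15.2 points.
- Six covariates at r = 0.3 (R² = 6 × 0.09 = 0.54): 58.8% against 87.2%, a gap of 28.4 points.

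**4. Why the distortion is conservative.** Take one covariate at R² = 0.3 under the null. It enters in 5.01% of trials. In those trials the unadjusted test would reject 19.6% of the time and the adjusted test rejects 4.6%. Overall: 0.0496 − 0.0501 × (0.196 − 0.046) = 0.0421. The rule removes some false positives and leaves the rest of the unadjusted analysis as it was.

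**5. With baseline stress in the model.** At correlation 0.80, baseline explains 0.80² = 64% of follow-up variance. The outcome is analysed with baseline as a covariate, 39 per arm.

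(a) Demographics equally related to baseline and follow-up; true difference 0.35 SD, which is 0.35/√(1 − 0.64) = 0.58 residual SD; 6,000 trials:

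| Covariates | Power, rule | Power, pre-specified | Type I error, rule | Type I error, pre-specified |
|---|---|---|---|---|
| 2, r = 0.4 | 71% | 72% | 4.2% | 4.3% |
| 6, r = 0.3 | 71% | 74% | 4.7% | 4.9% |
| 3, r = 0.2 | 70% | 70% | 5.5% | 5.5% |

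The Monte Carlo standard error of each type I figure is √(0.05 × 0.95/6000) = 0.28 points. A second simulation with baseline in the model put the power gap between about −1 and +2 points and type I error at about 5%.

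(b) Three demographic covariates sharing 0.1, 0.2 or 0.3 of the *residual* variance (0.036 to 0.108 of total variance, since 0.36 remains); difference 0.6 residual SD: power 0.75, 0.73, 0.74 under the rule against 0.78, 0.81, 0.86 pre-specified, gaps of about 3, 8 and 12 points. Some covariate entered in only 3 to 6% of trials.

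**The case against.** The strongest reply is that the large losses come from a model that the trial may not use. Section 2.6 specifies a repeated measures analysis, section 2.4 collects surveys from Time 0 to Time 4, and the rule does not screen baseline stress. If Time 0 stress is in the model, most of what demographics could add is already captured (step 5a). If the tested effect is a group-by-time contrast, a time-constant demographic main effect leaves it unchanged with complete data. Most of this stands, and the larger figures cannot be presented as this trial's loss. It is not a full answer. The article does not say which effect is tested. The average over visits best matches its sample size, and there demographics would matter more. Step 5b also shows a loss if demographics explain residual variance.

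A reader might infer that the rule inflates false positives, or that it loses nearly all the precision available from baseline data. Neither is supported: every departure attributable to the rule is conservative, and only demographic covariates are covered. The calculations do not cover an analyst choosing freely among unlisted covariates.

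It can also be said that when nothing is admitted, the model without demographics is valid. That is true, and it limits the harm. Finally, naming the covariates is commonly left to a statistical analysis plan. The absence of a list is therefore not the point here; the point is the stated rule, which a plan with pre-specified covariates would contradict.

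**Conclusion.** The rule is badly fixed and should be replaced, but it does not threaten the validity of a positive result. It selects on chance imbalance, makes the model depend on outcome and arm data, and in practice gives the unadjusted analysis.

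- **Power cost without baseline stress:** roughly 2 to 28 points for R² from 0.1 to 0.54.
- **Power cost with baseline stress at correlation 0.80:** about 0 to 3 points if demographics act equally on baseline and follow-up, and about 3 to 12 points if they explain 0.1 to 0.3 of residual variance.
- **Type I error:** about 3.5 to 4.7% without baseline stress and about 5% with it.

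These rest on 39 per arm, 0.05 screening thresholds, independent covariates and assumed R² values. The article gives only the first. The chance argument applies to differences at randomisation; differences among completers could also reflect dropout.

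**What to change.** Delete the significance rule. Before any Phase II outcome is seen, fix baseline PSS plus a short list of demographic covariates chosen on prior grounds. Include them whatever the observed imbalance or significance. Describe baseline balance without tests. The list itself can sit in the statistical analysis plan, provided that the two documents agree.

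The cost is one sentence of text and a few degrees of freedom. If the listed covariates turn out not to be prognostic, the loss is about 0.4 points of power with one covariate and about 2 with five (step 3, R² = 0), which is the reason to keep the list short. Sample size, conduct and data collection do not change.

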## Discussion

3

This two-phase study will be the first application of nature experience intervention using VR in family caregivers of HSCT recipients. The phase I study is a single-arm pre-post trial to evaluate the feasibility and acceptability of the four-week nature-based immersive VR program, and the phase II study is a prospective randomized controlled trial to test the effectiveness of the intervention on caregivers’ stress and symptoms. Existing interventions developed to relieve stress and symptoms in family caregivers usually required a great deal of time and effort from participants who may find it difficult to be away from their care recipients (50). Incorporating VR technology into stress reduction activities will provide family caregivers with immersive experiences by allowing them to experience real pleasant locations or realities without leaving the care recipient’s side. Studies have demonstrated novel applications of VR in various clinical scenarios. In particular, experiencing nature in a virtual environment was effective in reducing stress and psychological symptoms (e.g., pain and anxiety) (10, 13, 14). The application of nature environments implemented through VR is ideal for family caregivers with mobility and time constraints, who may have limited access to the nature environment in their real life and less opportunity to engage with nature. To our knowledge, limited studies have developed and tested interventions using VR in family caregivers. In this study, we expect that HSCT caregivers can take a break from their surroundings while experiencing restorative nature through immersive VR.

Despite the innovativeness and strengths of this study, a few limitations should be noted. First, only family caregivers of people receiving allogeneic HSCT at the NIH Clinical Center, a unique clinical research hospital setting providing care to those enrolled in research protocols with no charge to the research participants, are recruited to the study; thus, generalizability may be limited with respect to caregivers of other disease groups or patients receiving traditional care in general hospitals or clinics. Furthermore, this study recruits only English-speaking caregivers, which ultimately may limit generalizability to caregivers of other racial or ethnic backgrounds. In addition, in this study, once each participant is randomly assigned, the participant will be aware of the group assignment status. Therefore, the expectancy effect is not avoidable, which might influence participant behavior and the outcomes. A double-blind RCT design should be considered to get a more concise estimate of the specific effects of the intervention in the future. Lastly, this study will only examine the short-term effects (four weeks) of the intervention on stress and symptoms. Therefore, any longer-term effects of the nature-based VR intervention could not be captured in the present study. A more prolonged follow-up could further inform the long-term intervention effects in future trials and large-scale efficacy testing.

The nature-based immersive VR program has great potential to relieve stress and symptoms in family caregivers by providing the sense of being in real exposure to nature or outdoor environments, ultimately offering a source of respite for caregivers. Furthermore, by using objective biomarkers and validated self-report measures together, we will be able to assess the effects of our intervention comprehensively and accurately. Findings of this study will shed light on the use of nature-based VR intervention in caregiver populations across the spectrum of medical and psychological conditions. If proven feasible and effective, the nature-based VR program could be implemented to provide a convenient, attractive, and easily applied intervention to alleviate stress and symptoms in family caregivers at any time and place, differentiated from existing stress reduction interventions. Our findings will provide a foundation for future studies in diverse caregiver groups in terms of patient diagnosis and social determinants of health (e.g., age, sex, ethnicity). In addition, healthcare providers may recommend integrating the VR technology into clinical practice for both patients and their caregivers. The finding will lay the groundwork for the future study, in which we will aim to consider both patients and their caregivers to reduce their stress and stress-related symptoms.

## Ethics and dissemination

4

This research protocol was approved by the NIH Clinical Center Institutional Review Board. Informed consent will be obtained from all study participants.
